## **4 STATISTICS AND METHODOLOGY**

### **4.1 Statistical analysis plan**

#### **4.1.1 Sample size calculation**

For work package 1, assuming that 67% of patients will be categorized as high risk and 33% as low risk based on the simplified Geneva score, and assuming that the 90-day incidence of HA-VTE is 2.8% in high risk and 0.6% in low risk patients with and without TPX, we will need 1308 patients to detect an absolute risk difference of 2.2%, with a power of 80% at a 2-sided alpha of 0.05. The numbers stated above correspond to a relative risk of 4.7, a sensitivity of 90%, and a specificity of 34%. This sample size will provide sufficient precision for the validation of the simplified Geneva score. Assuming an area under the curve (AUC) of 0.75, the normal-approximation 95% confidence interval (CI) will range from 0.64 to 0.86. For sensitivity and specificity, the 95% Wilson CIs will range from 72% to 96% and from 31% to 36%, respectively. We will recruit 1350 patients to account for potential dropouts, which will be few given the low follow-up burden.

In work package 2, we will assess the same measures of association and prognostic accuracy as in work package 1, but using immobility measures rather than the RAMs, or a combination thereof. The sample size of 1350 patients will provide comparable precision as stated above.

#### **4.1.2 Statistical analyses**

Work package 1) Time to event analyses with competing risk methods will be used to assess the prognostic performance of the simplified Geneva score and the other RAMs (**Table 1**) and their association with HA-VTE, with non-VTE death representing the competing risk. We will use a subdistribution hazard model of Fine and Gray to assess the association of the simplified Geneva score and the other RAMs with VTE, calculating subhazard ratios with 95% CIs. These analyses will be adjusted for the use of TPX and study site. Cumulative incidences of HA-VTE in low- and high-risk score patients will be assessed and graphically presented to assess calibration and compare different RAMs. The time-dependent area under the curve (AUC) as well as sensitivity, specificity, and positive and negative predictive values will be calculated for each RAM to assess their accuracy to predict HA-VTE at 90 days using time-dependent receiver operating characteristic (ROC)-curve analysis, taking into account censored data and competing events. Additionally, because some patients will be treated with TPX and thus have a lower risk of VTE, we will perform separate sensitivity analyses in patients with and without TPX. It is possible that a small number of patients will be started on therapeutic dose anticoagulation for reasons other than VTE (e.g. new onset atrial fibrillation) during follow-up; these patients will be censored in the main analysis.

Secondary time-to-event outcomes (major and clinically relevant non-major bleedings) will also be evaluated using competing risk regression. For all-cause mortality, we will use an ordinary Cox regression, for length of stay an accelerated failure time model. Binary outcomes (in-hospital VTE and readmission) will be evaluated using logistic regression. The Barthel-index will be assessed using linear regression. All models will be adjusted for the use of TPX and study site.

Work package 2) We will examine the association between subjective (physician's perception) and objective (accelerometry-measured) mobility levels, as a continuous measure as well as divided into quartiles, and 90-day cumulative incidences of HA-VTE using competing risk regression (accounting for non-VTE related death as a competing event), unadjusted as well as adjusted for TPX and study site. To define an optimal cutoff for objective immobility, we will assess sensitivity and specificity at different mobility levels using time-dependent ROC-curve analysis accounting for censored data and competing events. To compare the predictive performance of the simplified Geneva score using the standard subjectively-assessed definition of immobilization (i.e. physician perception) versus using objective accelerometry-assessed mobility measures, we will use likelihood ratio tests and/or the Akaike information criterion (AIC) as well as the c-statistics in competing risk models; immobility measures will be used as single covariates, as well as incorporated in the simplified Geneva score. We will assess the net reclassification index to assess improvement in risk prediction if using the accelerometry-based instead of the subjective immobility measure for the simplified Geneva score.

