## 1.2 Relevance, Originality, and Perspectives

In accordance with a call for more research on VTE risk assessment, our study **explores novel risk stratification strategies** for HA-VTE in medical inpatients using accelerometry-assessed immobility and examines the validity of a new easy-to-use RAM, the simplified Geneva score.

There is a lack of objective information on mobility and its level-dependent impact on VTE in medical inpatients, limiting the ability of physicians to estimate the degree of a patient's mobility or immobility to inform the decision on TPX prescription. Thus, the use of a tracking device to record and monitor daily steps for measuring mobility during hospital stay is **innovative** and may reflect patient mobility more accurately than standard subjective methods of mobility assessment. If our study can establish an objectively measured immobility level at which inpatients would be at higher risk of HA-VTE, increasing patient mobility above this threshold could be a simple and safe novel VTE prevention strategy.

Moreover, our project will provide the **first prospective head-to-head comparison** of validated VTE RAMs. The current uncertainty about optimal provision of TPX and the underuse of RAMs due to their complexity is reflected by the fact that only about 40% of high risk patients receive appropriate TPX, while it is inappropriately provided in almost half of all low risk patients, resulting in unnecessary bleeding events and costs. Our results will provide a clear guidance for physicians about optimal VTE risk assessment and thus have the potential to **facilitate and improve VTE prevention** and reduce HA-VTE and associated deaths in medical inpatients.

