#### Objectives of work package 1: Evaluate current VTE risk prediction strategies

- 1) to prospectively validate the simplified Geneva score as a RAM to predict HA-VTE (primary objective)

**Assumption:** *the novel, easier-to-use simplified Geneva score will be able to accurately detect medical inpatients at risk of HA-VTE (primary hypothesis)*

- 2) to compare the prognostic performance of the simplified Geneva score to discriminate between low and high VTE risk patients with previously validated RAMs (original Geneva, Padua, and IMPROVE score)

**Assumption:** *the novel, easier-to-use simplified Geneva score will be at least as accurate as previously validated RAMs in detecting medical inpatients at risk of HA-VTE*

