## Autonomy

Modified Barthel Index; location of eating, eliminating urine or stool, and washing

Comorbidities will be collected according to the Charlson Comorbidity Index.

Autonomy in the activities of daily living prior to hospitalization will be assessed at admission using the modified Barthel Index in a face-to-face interview (for description of the modified Barthel Index, see section 2.2.3). For patients with cognitive impairment or confusion, the level of autonomy before hospitalization will be assessed by interviewing their relatives or caregivers, in face-to-face interviews or by phone call.

Data will be collected from electronic health records, except for information such as data on contact details, mobility, paresis/paralysis, recent travel, dehydration, leg, edema, and patient autonomy, which will be collected at the patient bedside (from the patient and/or nurse in charge) by trained study nurses.

At baseline, the simplified and original Geneva score, the IMPROVE score, and the Padua score will be calculated and patients will be categorized as high or low VTE risk according to each RAM (**Table 1**). Treating physicians will not be informed of the patients' scores, and no specific recommendations concerning the use of a RAM or TPX will be made. Thus, the use of TPX will not be influenced by the study.

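### Work package 1 objective 2 compares four risk scores, but section 4.1.2 lists only per-score estimates and a plot, with no paired between-score difference

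*Protocol*

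**What the plan says.** Protocol section 2.1 sets the second objective of work package 1 as "to compare the prognostic performance of the simplified Geneva score to discriminate between low and high VTE risk patients with previously validated RAMs", namely the original Geneva, Padua and IMPROVE scores. Under the label Assumption it adds that the simplified Geneva score "will be at least as accurate as previously validated RAMs in detecting medical inpatients at risk of HA-VTE". Section 1.2 presents the project as the "first prospective head-to-head comparison" of validated RAMs and expects the results to help identify the most accurate one for a future trial's eligibility criteria.

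Section 3.3.3.1 (under Autonomy) makes the data paired: "At baseline, the simplified and original Geneva score, the IMPROVE score, and the Padua score will be calculated and patients will be categorized".

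For work package 1, section 4.1.2 lists:

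- Fine-Gray models for each RAM, "calculating subhazard ratios with 95% CIs";
- cumulative incidences in low- and high-risk patients, "graphically presented to assess calibration and compare different RAMs";
- time-dependent AUC, sensitivity, specificity and predictive values, which "will be calculated for each RAM to assess their accuracy to predict HA-VTE at 90 days".

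For work package 2, the same section names comparison statistics: likelihood ratio tests and/or AIC, c-statistics and the net reclassification index. The synopsis adds no contrast for work package 1. Section 4.1.1 gives precision for the simplified Geneva score alone, not for a difference between scores.

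**The concern.** The objective is a comparison, and its expectation has the form of a non-inferiority statement. That calls for an estimate of how much worse the simplified Geneva score could be than each competitor. The listed outputs describe each score separately. The plotted incidence curves are the only work package 1 item said to compare RAMs, and they carry no estimate of a difference in accuracy.

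Two things are at stake. First, separate summaries discard the pairing, which is the main source of precision for this comparison. Second, objective 2 has no stated quantity from which a conclusion can be drawn, although the protocol promises physicians guidance on which RAM to use. Section 4.1 carries the title of a statistical analysis plan and names comparative statistics for work package 2, so their absence for work package 1 is a mismatch between a stated objective and its stated method.

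**Working it through.** **Inputs from section 4.1.1:** N = 1308; 67% high risk and 33% low risk; 90-day HA-VTE 2.8% and 0.6%; AUC 0.75 with 95% CI 0.64 to 0.86.

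**Assumptions not in the protocol:** every RAM has AUC 0.75; the correlation r between two AUC estimates from the same patients is 0.5 to 0.9; deficits of 0.05 and 0.10 serve as yardsticks. The formula ignores censoring and competing events.

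**Step 1, events.** 1308 × (0.67 × 0.028 + 0.33 × 0.006) = 27.1 events and 1280.9 non-events.

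**Step 2, reproduce the plan's AUC interval (Hanley-McNeil).**

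- Q₁ = A/(2 − A) = 0.75/1.25 = 0.600
- Q₂ = 2A²/(1 + A) = 1.125/1.75 = 0.643
- SE² = [A(1 − A) + (events − 1)(Q₁ − A²) + (non-events − 1)(Q₂ − A²)] / (events × non-events)
- SE = 0.0547; half-width 1.96 × 0.0547 = 0.107; interval 0.643 to 0.857

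This matches the stated 0.64 to 0.86.

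**Step 3, difference between two AUCs.** SE_diff = SE × √(2(1 − r)). If pairing is ignored (r = 0), SE_diff = 0.0774 and the half-width is 0.152.

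**Step 4, chance that the lower 95% limit excludes a deficit m when the true difference is zero.** P = Φ(m/SE_diff − 1.96).

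| Assumed r | SE_diff | 95% half-width | P, m = 0.05 | P, m = 0.10 |
|---|---|---|---|---|
| 0.5 | 0.0547 | 0.107 | 15% | 45% |
| 0.7 | 0.0424 | 0.083 | 22% | 66% |
| 0.8 | 0.0346 | 0.068 | 30% | 82% |
| 0.9 | 0.0245 | 0.048 | 53% | 98% |

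At the full 1350 patients (28.0 events) the half-width is 0.106 at r = 0.5 and 0.047 at r = 0.9, so the picture does not change.

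**Step 5, what limits the comparison.** For 80% probability of excluding a 0.05 deficit, the same formulas require about 12,286 patients at r = 0.5, 7,372 at 0.7, 4,915 at 0.8 and 2,458 at 0.9. Pairing narrows the interval considerably, but with about 27 events a tight margin is out of reach over this range of r.

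**The case against.** The strongest reply is that the method for comparing correlated AUCs is ordinary SAP content. Section 4.1.2 already fixes the accuracy measures, the 90-day horizon and the handling of censoring and competing events, and nothing in it rules out a paired contrast. The sentence on accuracy is labelled an assumption. Only the one attached to objective 1 is marked as the primary hypothesis, and objective 2 has no margin, alpha or power, so it can be read as an expectation behind a descriptive comparison. Much of this stands. It makes the point a modest one about a non-primary objective and makes a descriptive label an acceptable remedy. It does not remove the mismatch, because the same section names comparative statistics for work package 2 and, for work package 1, names a plot.

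A reader might infer two stronger things that the protocol does not support:

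- **That the expectation cannot be supported at all.** All four scores are collected in every patient, so a paired contrast needs no new data, and a separate SAP could specify it.
- **That the investigators plan to conclude similarity from overlapping intervals or a non-significant result.** Section 4.1.2 states no such rule. It mentions confidence intervals only for the subhazard ratios, not for the AUCs.

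It is also fair to object that the size depends on an assumed correlation. The scores share many items (Table 1), so r may be high, particularly between the two Geneva scores. This is why the range runs to 0.9.

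**Conclusion.** The point holds in a limited form. For objective 2 of work package 1, section 4.1.2 gives per-RAM estimates and a plot, and no between-RAM contrast. Those analyses do not by themselves address the expectation that the simplified Geneva score is no less accurate than the others. A paired AUC difference would have a 95% half-width of about 0.11 to 0.05, rather than 0.15 with pairing ignored.

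Pairing alone would not secure a strong claim. Whether a deficit of 0.10 could be excluded depends heavily on the correlation, and a deficit of 0.05 would at best be excluded about half the time. These figures rest on the protocol's event rates, equal AUCs of 0.75, an assumed r of 0.5 to 0.9, and a variance formula without censoring or competing events. The primary objective is unaffected.

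**What to change.** In section 4.1.2, for the simplified Geneva score against each of the other three RAMs, add:

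- the paired difference in 90-day time-dependent AUC;
- the paired differences in sensitivity and specificity at the Table 1 cut-offs;
- 95% confidence intervals that respect the pairing, for example from a bootstrap that resamples patients.

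State the objective 2 conclusion as the largest deficit that the lower limit excludes. Alternatively, label the comparison descriptive and drop the expectation that the score is no less accurate. Either change should be made before results are seen.

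The cost is a small amount of analysis code and one table, with no new data or patients. The downside is that the claim for this secondary objective will probably become weaker.

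### In-hospital VTE is assigned plain covariate-adjusted logistic regression although the protocol's own rates imply so few events that a high-versus-low odds ratio may not be finite

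*Protocol*

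**What the plan says.** Section 2.2.2 lists symptomatic, objectively confirmed HA-VTE during the hospital stay among the secondary outcomes. Section 4.1.2 gives one method for this outcome and for readmission: "Binary outcomes (in-hospital VTE and readmission) will be evaluated using logistic regression". It then adds: "All models will be adjusted for the use of TPX and study site". Section 2.3 plans three or more hospitals, so site takes at least two indicator terms. With one term for the score and one for TPX, the model has at least four slopes.

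The only event rates are the 90-day ones in section 4.1.1, which assumes that "67% of patients will be categorized as high risk and 33% as low risk" and that "90-day incidence of HA-VTE is 2.8% in high risk and 0.6% in low risk patients". The protocol gives no in-hospital incidence, no expected in-hospital event count and no share of the 90-day events occurring in hospital. It names no method for sparse events. It does not say whether the score enters this model as high/low or as points, although section 3.3.3.1 has patients categorised as high or low risk on each score.

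**The concern.** One method covers two binary outcomes, and the rates in section 4.1.1 make one of them rare. If the low-risk group has no in-hospital event, the likelihood keeps rising as the high-versus-low log odds ratio grows, so no finite maximum-likelihood estimate exists. A Wald interval is then meaningless. Analysts would have to change the estimator, or report something other than the stated odds ratio, at a time when they can see the data, unless a method had been fixed beforehand. Even without an empty group, four or more slopes on a handful of events give an unstable fit.

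**Working it through.** **Inputs from the protocol.** High/low split 67%/33%; 90-day incidence 2.8% and 0.6%; 1308 patients required and 1350 recruited (all section 4.1.1); at least three sites (section 2.3).

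**Input not in the protocol (assumption).** s, the share of 90-day HA-VTE events that occur in hospital. One third to one half is used as the main range, with one quarter to all shown around it.

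**1. Reproduce the plan's own figure.** Two proportions, pooled variance under the null, no continuity correction, 80% power, two-sided alpha 0.05. Pooled risk = 0.67 × 0.028 + 0.33 × 0.006 = 0.0207. This requires 435 low-risk patients, a total of 435 / 0.33 ≈ 1318, within 1% of the stated 1308. Power at 1308 is 79.7%. The stated rates can therefore be taken as the plan's working rates.

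**2. Events over 90 days in 1350 patients.**
- High risk: 1350 × 0.67 × 0.028 = 25.3
- Low risk: 1350 × 0.33 × 0.006 = 2.7
- Total: 28.0

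As a check, 25.3 / 28.0 = 90%, the sensitivity that section 4.1.1 quotes.

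**3. Chance of no low-risk in-hospital event.** The low-risk group has 1350 × 0.33 ≈ 446 patients. With in-hospital risk 0.006 × s, the probability is (1 − 0.006 × s)^446.

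| Share s (assumed) | In-hospital events | Low-risk events | P(no low-risk event) |
|---|---|---|---|
| 1/4 | 7.0 | 0.67 | 0.51 |
| 1/3 | 9.3 | 0.89 | 0.41 |
| 1/2 | 14.0 | 1.34 | 0.26 |
| 3/4 | 21.0 | 2.00 | 0.13 |
| 1 | 28.0 | 2.67 | 0.07 |

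**4. Events per slope.** With four slopes: 9.3 / 4 = 2.3 at one third, 14.0 / 4 = 3.5 at one half, and 28.0 / 4 = 7 if every event is in hospital.

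**5. What Firth's method would give.** For an unadjusted 2×2 table, Firth's estimate equals adding 0.5 to each cell. Simulated tables with 904 high-risk and 446 low-risk patients, true odds ratio 4.7:

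| | s = 1/3 | s = 1/2 |
|---|---|---|
| Firth, all runs (always finite), median | 3.5 | 3.8 |
| Maximum likelihood, runs with a low-risk event, median | 3.0 | 4.0 |
| Firth, the same runs, median | 2.3 | 3.1 |

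The last two rows compare like with like. There, Firth's median is further from 4.7 than that of maximum likelihood. Firth's gain is that an estimate and interval exist in every study. It does not bring the typical estimate nearer the truth.

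**The case against.** The case on the other side has several parts.

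- **The event count is assumed.** A reader might infer that the protocol predicts 9 to 14 in-hospital events. It does not. It gives 90-day rates only, and the chance of an empty low-risk group runs from 7% to 51% over the shares shown. This stands, and the result must stay conditional.
- **The score may enter as points.** A reader might infer that the problem arises however the score is coded. With points, an empty low-risk group does not by itself make the odds ratio infinite. This stands. The high/low reading is plausible because section 3.3.3.1 categorises patients that way and the sample size rests on that contrast, but section 4.1.2 does not settle it for this model.
- **The text does not say ordinary or maximum-likelihood.** Section 4.1.2 uses the word ordinary for the Cox model, not for the logistic one, and a separate analysis plan, not shown, could specify a penalised or exact version. This stands in part. Unqualified logistic regression is normally read as maximum likelihood, and the protocol names it under its own analysis-plan heading for data that its own rates show to be sparse. Whether a change of method would really come after the data are seen cannot be known from this document.
- **Empty site or TPX levels.** A reader might add these to the failure rate. With three equal sites, the chance that some site has no event is about 3 × (2/3)^9.3 = 7%, or 3 × (2/3)^14 = 1%. In that case the site coefficient diverges while the score's odds ratio can stay finite, so these cases do not belong in the headline figure.
- **Something usable would remain.** With no low-risk event, a likelihood-ratio test, a one-sided profile-likelihood limit and the raw counts are still available. To say that the outcome could not be reported would be too strong.

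**Conclusion.** The point holds in a limited form. The protocol's rates imply about 28 HA-VTE events over 90 days, 2.7 of them low-risk, and the in-hospital outcome draws on only part of these. If one third to one half occur in hospital and the score enters as high/low, plain logistic regression would give an infinite odds ratio in about 41% to 26% of studies. The range is 51% to 7% for shares from one quarter to all.

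This concerns one secondary outcome for which the study was not sized. The primary 90-day analysis uses competing-risk regression and time-dependent ROC methods and is not touched. A reader might also infer that maximum likelihood is too biased here and that Firth corrects it; the like-for-like comparison does not support that. What remains is a cheap improvement: settle in advance a method that yields an estimate and interval whatever the counts turn out to be.

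**What to change.** In section 4.1.2, separate the two binary outcomes. For in-hospital VTE, replace plain logistic regression with Firth penalised-likelihood logistic regression with profile-likelihood confidence intervals, keep TPX and study site as covariates, and report the number of events in each risk group beside the estimate. Keep ordinary logistic regression for readmission.

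The cost is one clause and standard software; no extra data or patients are needed. The statistical price is shrinkage towards the null, which is material at these event counts (median about 3.5 to 3.8 against a true 4.7) and should be acknowledged when the result is read.

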#### Objectives of work package 2: Assess novel VTE risk prediction strategies using objective measures of mobility

- 1) to assess whether objective accelerometry-assessed immobilization predicts the risk of HA-VTE and to compare it to the standard subjective method to assess immobilization (physician perception)

**Assumption:** objective, accelerometry-assessed immobilization will be more accurate in predicting the risk of HA-VTE than subjective physician perception.

- 2) to compare the predictive performance of the simplified Geneva score using the standard subjectively-assessed definition of immobilization (i.e. physician perception) versus using objective accelerometry-assessed mobility measures

**Assumption:** the incorporation of accelerometry-assessed immobility into the simplified Geneva risk score will improve its prognostic performance

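### On the natural reading of work package 2, the cut-off-based comparisons are biased towards accelerometry, because its cut-off is chosen and judged on the same 27 to 28 expected events

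*Protocol*

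**What the plan says.** Section 4.1.2, work package 2, contains three relevant steps, all in the one cohort.

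- Association: subjective and objective mobility are related to 90-day HA-VTE, in continuous form and in quartiles.
- Cut-off: "To define an optimal cutoff for objective immobility, we will assess sensitivity and specificity at different mobility levels using time-dependent ROC-curve analysis".
- Comparison: the simplified Geneva score with physician-perceived immobility is set against the score with accelerometry-assessed immobility, by likelihood ratio test and/or AIC and by c-statistic. The measures are used alone and inside the score. The section adds: "We will assess the net reclassification index to assess improvement in risk prediction if using the accelerometry-based instead of the subjective immobility measure".

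The hypothesis in Section 2.1 is that "the incorporation of accelerometry-assessed immobility into the simplified Geneva risk score will improve its prognostic performance".

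Three other places matter. Table 1 gives immobilization 2 points in the simplified Geneva score as a present/absent item, with high risk at 3 points or more. Section 3.3.3.2 fixes the physician's Geneva item in advance (bedrest, or inability to walk more than 30 minutes a day, for at least 3 days). The same section lists several accelerometry measures and names none as the one to be used. Its only preset threshold, 4 steps per minute, classifies minutes and not patients. On precision for work package 2, Section 4.1.1 says: "The sample size of 1350 patients will provide comparable precision as stated above".

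**The concern.** A cut-off picked because it separates events from non-events best in a data set looks better in that data set than it is. If only one of two competing measures is tuned this way, the optimism does not cancel: it is credited to the tuned measure. Here that is accelerometry, the measure the protocol expects to win. AIC gives no protection, since a searched cut-off is not counted as an extra parameter. With few events the effect is not small.

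At stake are the second objective of work package 2 and the cut-off-based part of the first. Section 1.2 also intends the mobility threshold to inform an intervention in a future randomised trial, so an over-optimistic threshold would carry forward.

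**Working it through.** **Inputs (Section 4.1.1).** The risk split is stated as "assuming that 67% of patients will be categorized as high risk and 33% as low risk based on the simplified Geneva score"; the risks as "the 90-day incidence of HA-VTE is 2.8% in high risk and 0.6% in low risk patients with and without TPX"; the size as "we will need 1308 patients to detect an absolute risk difference of 2.2%, with a power of 80% at a 2-sided alpha of 0.05"; and then "We will recruit 1350 patients to account for potential dropouts".

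**1. Reproduce the plan's figure.** Two proportions, pooled variance, no continuity correction, high:low ratio k = 2:

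n(low) = [1.96·√((1+1/k)·p̄(1−p̄)) + 0.8416·√(p₁(1−p₁) + p₂(1−p₂)/k)]² / (p₂−p₁)²

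With p₁ = 0.006, p₂ = 0.028 and p̄ = (0.006 + 2×0.028)/3 = 0.02067, this is (0.3415 + 0.1177)² / 0.022² ≈ 436. Then 436 × 3 = 1308, as stated. The exact 67/33 split gives 1318.

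**2. Expected events.** Overall risk = 0.67×0.028 + 0.33×0.006 = 0.02074. Events = 1308 × 0.02074 = 27.1, or 1350 × 0.02074 = 28.0.

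**3. Simulate the tuned-versus-fixed comparison.** Two normally distributed markers have the same true AUC. The physician marker is dichotomised at a fixed cut-off. The accelerometry marker is dichotomised at the cut-off that maximises the Youden index J (sensitivity + specificity − 1) in the same data. For a binary item, AUC = (1+J)/2. The outcome is binary at 90 days, without censoring or competing death. Youden columns: N = 1350, 28 events. Other columns: N = 1308, 27 events on average, accelerometry minus physician, with the share of runs favouring accelerometry.

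| True AUC of both | Apparent J | True J at chosen cut-off | Inflation | Score AUC gap | NRI at ≥3 points | Continuous AUC gap |
|---|---|---|---|---|---|---|
| 0.50 | 0.115 | 0.000 | 0.115 | +0.033 (82%) | +0.024 (61%) | −0.002 (49%) |
| 0.60 | 0.229 | 0.124 | 0.105 | +0.024 (73%) | +0.019 (59%) | 0.000 (50%) |
| 0.65 | 0.292 | 0.195 | 0.097 | +0.021 (72%) | +0.018 (59%) | −0.002 (50%) |
| 0.70 | 0.364 | 0.269 | 0.095 | +0.018 (69%) | +0.016 (58%) | −0.002 (49%) |

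**4. Control.** With the accelerometry cut-off fixed in advance, the score AUC gap is −0.002 to +0.001, the NRI −0.003 to +0.001, and accelerometry looks better in 48% to 52% of runs. The bias therefore comes from the tuning.

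**5. Dependence on events and on the number of measures.** At AUC 0.65 the item-level AUC gap falls from 0.038 with 28 events to 0.009 with 280. If the best of 4 to 8 measures (assumed correlation 0.5) is also picked, the item-level gap is 0.07 to 0.09, in 89% to 93% of runs.

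**6. Does a bootstrap that repeats the search help?** With 100 resamples in each of 400 simulated studies, the item-level AUC gap falls from 0.029–0.036 to 0.001–0.006 for true AUC 0.60 to 0.70 (50% to 51% of runs favour accelerometry). For an uninformative marker it falls from 0.051 to 0.017 (60% of runs). The corrected J still lies about 0.03 above the true J at the chosen cut-off in each setting (for example 0.226 − 0.196 = 0.030), so the correction is good but incomplete.

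**The case against.** - **The protocol does not say that the ROC-selected cut-off enters the score.** This is correct. It says only that immobility measures will be incorporated. The inference rests on the item being yes/no, and on the ROC-derived threshold being the only patient-level threshold the protocol provides for. The point stands as the natural reading, not as stated text.
- **No search over several measures is planned.** Also correct. A reader might infer one from the list in Section 3.3.3.2, but Section 4.1.2 speaks of a single optimal cut-off. The protocol leaves the search open and does not announce it.
- **Cut-off-free analyses are already planned.** They are, in continuous and quartile form, and the cut-off selection does not touch them. Section 3.3.3.2 also collects a graded physician estimate, so the first objective is not only a tuned binary item against a fixed one.
- **Internal validation may be in the SAP.** The SAP is not at hand, and it would be wrong to conclude that none will be done. But the protocol commits to an asymmetric derive-and-compare procedure, and its precision statement for work package 2 makes no allowance for selecting a threshold.
- **Work package 2 is not the primary objective.** True, and it limits the severity.

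**Conclusion.** The concern holds for the cut-off-based comparisons, on the natural reading that the selected cut-off becomes the score item. The bias is one-sided and points towards the protocol's own hypothesis. With one measure and 27 to 28 expected events, it is about 0.09 to 0.12 on the apparent Youden index, 0.02 to 0.03 on the score AUC and 0.02 on the NRI; it is larger if several measures are searched.

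A reader might infer that accelerometry will appear to win even when the two measures are equally good. The figures do not support that. With one measure it is a tendency, in 69% to 82% of runs on score AUC and 58% to 61% on NRI. Nor is the whole of work package 2 compromised, since the continuous and quartile analyses are unaffected.

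Assumptions not taken from the protocol: normal markers, true AUC 0.50 to 0.70, a Youden-maximising choice (the protocol does not define optimal), the distribution of the other score items, and no censoring or competing death.

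**What to change.** In Section 4.1.2:

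1. Name one accelerometry measure before outcomes are seen.
2. Make its continuous form the primary objective-versus-subjective comparison.
3. State which threshold enters the score. Label the ROC-derived cut-off, and the c-statistic and NRI comparisons that use it, exploratory.
4. Repeat the whole selection (cut-off and, if searched, measure) and the rebuilding of the score within each bootstrap sample. Report optimism-corrected differences in AUC, sensitivity, specificity and NRI with confidence intervals.

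In Section 4.1.1, qualify the precision statement: work package 1 validates a ready-made score, whereas work package 2 derives a threshold.

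Taking the Geneva definition's 30 minutes of walking a day as a ready-made accelerometry cut-off is tempting but not advised. Section 1.1 cites 7 minutes of walking a day in 100 older patients, so it could class most older inpatients as immobile. It would also ignore the 3-day element of the definition.

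The cost is a paragraph, some analysis code and less favourable reported performance. Because the bootstrap leaves some bias at about 27 events, most clearly when the marker is uninformative, prespecification should come first.
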